## Abstract

**Background:**

Trimetazidine is a metabolic anti-ischemic agent, which increases the tolerance of cardiomyocytes to ischemia. However, few studies have explored the effect of trimetazidine on ventricular remodeling in coronary artery disease (CAD) patients undergoing percutaneous coronary intervention (PCI) with left ventricular hypertrophy (LVH).

**Methods:**

It is a randomized, placebo-controlled trial, and we propose to recruit one hundred and twenty-four CAD patients undergoing PCI with LVH during a 12-month period. They will be randomized to receive either trimetazidine (35 mg twice a day) or placebo in the following 12 months after PCI. Blood tests, echocardiography, symptom of angina and major adverse cardiovascular events (MACEs) will be collected at follow-up visit at 3 and 12 months. The primary end point will be the left ventricular remodeling measured by left ventricular mass index (LVMI) at 3- and 12-month follow-up compared with the baseline. The secondary end points will be the symptom of angina assessed by Seattle Angina Questionnaire, myocardial ischemia measured by 6-min walk test and exercise electrocardiography test, as well as MACEs (defined as a composite of death, myocardial infarction, stroke, recurrent angina, re-hospitalization, change of viable myocardium).

**Discussion:**

This study aims to demonstrate the effect of trimetazidine on left ventricular remodeling and myocardial ischemia in CAD patients undergoing PCI with LVH. Trimetazidine treatment is likely to improve the left ventricular remodeling, symptoms of angina and myocardial ischemia. It might also reduce the risk of MACEs in CAD patients undergoing PCI with LVH.

**Trial registration:**

http://www.chictr.org.cn, Chinese Clinical Trial Registry (ChiCTR1800017876). Registered on 19 Aug 2018.

## Background

Coronary artery disease (CAD) has become the second leading cause of death after malignant tumor in China, with the prevalence of 6.46% [1, 2]. Left ventricular hypertrophy (LVH), an increase in muscle mass of left ventricle, has been identified as a powerful risk factor for future cardiovascular morbidity and mortality, with the risk of cardiovascular events increasing six-fold to eight-fold [3]. In addition, LVH is independently associated with a higher risk of all-cause mortality and a higher incidence of heart failure in CAD patients treated with percutaneous coronary intervention (PCI) [4–6]. LVH can develop myocytes death and fibrotic remodeling, and this promotes cardiac dysfunction [7], leading to cardiac hypoxia [8].

Besides, microvascular dysfunction is a recognized feature of hypertrophic cardiomyopathy and it may exacerbate myocardial ischemia in CAD patients [9]. Although PCI has become one of the leading treatment methods for coronary heart diseases, microcirculation disturbance and cardiac metabolic disorders caused by LVH still cannot be effectively relieved. Distinctive from other anti-anginal agents, trimetazidine is an anti-ischemic metabolic agent [10–12]. Trimetazidine optimizes the energy utilization of myocardial cells and maintains a proper energy supply during ischemia [13]. It protects the heart by inhibiting oxidative stress [14], scavenging oxygen free radicals [15, 16], improving lipid metabolism and mitochondrial function [14, 17], and reducing ionic imbalance during ischemia and reperfusion [18]. Researchers have reported the protective effect of trimetazidine in CAD patients undergoing PCI [19, 20]. However, its long-term effect on left ventricular remodeling in CAD patients undergoing PCI is still unclear.

This prospective randomized trial is therefore designed to explore whether trimetazidine can improve ventricular remodeling in CAD patients with LVH, as well as trying to investigate whether trimetazidine treatment can reduce major adverse cardiovascular events (MACEs). This study is to provide evidence for further clinical application of trimetazidine in CAD patients undergoing PCI with LVH.

## Methods/design

### Study design

It is the first prospective, placebo-controlled study to explore the relationship between trimetazidine and ventricular remodeling. CAD patients undergoing PCI with LVH will be randomized to receive trimetazidine (35 mg twice a day) or placebo for 12 months after PCI. Coronary intervention and other medication therapy will be performed according to current guidelines, and no difference in the use of angiotensin-converting enzyme inhibitor (ACEI), angiotensin receptor blocker (ARB) and aldosterone antagonist should be ensured between the two groups. The web-based randomization will be used for a 1:1 ratio grouping to either trimetazidine or placebo. Secretary of department of cardiology accesses the website via account password and is responsible for randomization. Block randomization will be stratified by concomitant medications (ACEI, ARB or aldosterone antagonist), sex and family history and it is blind to those who enroll participants or assign interventions. Blood biochemistry, echocardiography, Seattle Angina Questionnaire, 6-min walk test (6-MWT), exercise electrocardiography test and MACEs will be collected at the 3- and 12-smonth clinical follow-ups. All personal information will be converted to the new subject number. The attending physicians are responsible for data entry. Data monitoring committee is responsible for data security and accuracy. Committee members ([name], [name] and [name]) have access to the final dataset and periodically range check for data values.

The primary end point is the change of ventricular remodeling assessed by left ventricular mass index (LVMI) at 3- and 12-month follow-up after PCI compared with the baseline. The secondary end points will be the symptom of angina assessed by Seattle Angina Questionnaire, myocardial ischemia measured by 6-MWT and exercise electrocardiography test, as well as MACEs (defined as a composite of death, myocardial infarction, stroke, recurrent angina, re-hospitalization, change of viable myocardium). Details of the proposed study, including enrollment and follow-up visits, are outlined in Table 1. All serious adverse events must be reported to the sponsor immediately or within 24 h in case report forms (CRFs).

**Table 1 Tab1:** Study plan

Activity	Visit 0 screening	Visit 1	Visit 2
	0 day	3 months ±7 day	12 months ±7 day
Inclusion/exclusion criteria	×		
Informed consent	×		
Randomization	×		
Demography and medical history	×		
Physical examination	×	×	×
12-lead ECG	×	×	×
Concomitant medication	×	×	×
CBC	×	×	×
Scr, BUN, UA	×	×	×
ALT, AST	×	×	×
TC, LDL-C, HDL-C, TG	×	×	×
NT-proBNP	×	×	×
cTnT/cTnI	×		
Echocardiography	×	×	×
Symptoms of angina	×	×	×
6 min walk test	×	×	×
Exercise electrocardiography test	×	×	×
MACEs		×	×
Quality of life	×	×	×

*ECG* Electrocardiography, *CBC* complete blood count, *Scr* serum creatinine, *BUN* blood urea nitrogen, *UA* uric acid, *ALT* alanine aminotransferase, *AST* aspartate aminotransferase, *TC* total cholesterol, *LDL-C* low-density lipoprotein cholesterol, *HDL-C* how-density lipoprotein cholesterol, *TG* triglyceride, *NT-proBNP* N-terminal pro-B–type natriuretic peptide, *cTnT/cTnI* cardiac troponin-T/ cardiac troponin-I, *MACEs* major adverse cardiovascular events

The trial protocol has been approved by the Institutional Ethics Committee of Sir Run Run Shaw Hospital of Zhejiang University (KY20180508–25) and has been registered in at *Chinese Clinical Trial Registry* (ChiCTR1800017876). All patients will provide written informed consents before randomization.

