### Primary end point

The primary end point in this study is the change between baseline and follow-up LVMI (calculated as the ratio: left ventricular mass (LVM)/ body surface area). Two-dimensional and Doppler echocardiography will be performed to quantify left ventricular function and structure (Phillips Healthcare) [21]. Ventricular remodeling will be assessed by calculating LVMI using Devereux formula. Interventricular septum thickness (IVST), left ventricular end-diastolic dimension (LVEDd), left ventricular posterior wall thickness (LVPWT) will be measured by echocardiography. LVM = 1.04[(IVST + LVEDd + LVPWT)^3^-LVEDd^3^]-13.6 g.

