### Statistical considerations

#### Sample size

According to previous study [20], we hypothesized trimetazidine group has an effective rate of 70% to improve the left ventricular remodeling by reducing LVMI and placebo group has 40%, thus 56 patients in each group are necessary to offer 90% power at 0.05 significant level according to 1:1 ratio of random grouping. Anticipating 10% of patients potentially non-assessable according to previous experience on 12-month study, 124 randomized patients in total are needed.

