#### Analysis

The final results will be presented on an intention-to-treat (ITT) basis. All data will be presented as percentages or mean ± standard deviation (SD). The comparison of data will be performed using the Chi-squared test (categorical variables) or Student’s t test (continuous variables). Cumulative incidences of end points in 12 months after PCI will be calculated using Kaplan-Meier methods. Log-rank tests will be used for comparisons between groups. Possible covariables will be incorporated in the analysis if certain important baseline levels are still not matched after randomization. Mean imputation will be used to handle missing data. A *p*-value < 0.05 will be considered significant. All statistical analyses will be performed using the Statistical Package for Social Sciences (SPSS), version 20.0 (SPSS Inc., Chicago, IL, USA). The results will be published by chief investigator and major contributors.

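### The primary end point is LVMI change at both 3 and 12 months with one undivided 0.05 threshold, so no visit decides the trial and the false-positive rate of the primary claim is not fixed

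*Protocol article*

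**What the plan says.** The primary end point is described in three places in the protocol article.

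- Abstract, Methods: remodeling "measured by left ventricular mass index (LVMI) at 3- and 12-month follow-up compared with the baseline".
- Study design: "The primary end point is the change of ventricular remodeling assessed by left ventricular mass index (LVMI) at 3- and 12-month follow-up after PCI".
- Primary end point: "The primary end point in this study is the change between baseline and follow-up LVMI", with no visit given.

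The Study objectives section, which states the primary objective, names no visit either.

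The Analysis section says "The comparison of data will be performed using the Chi-squared test (categorical variables) or Student’s t test (continuous variables", and closes with one rule for all p-values: "< 0.05 will be considered significant". Neither test combines the two visits.

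The Sample size section assumes that "trimetazidine group has an effective rate of 70% to improve the left ventricular remodeling by reducing LVMI and placebo group has 40" percent. It asks for 56 patients per arm for 90% power at a 0.05 level, and 124 randomized after a 10% allowance for non-assessable patients. That is one comparison at one level.

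**The concern.** A primary end point measured at two visits needs a rule that turns two results into one conclusion. Possible rules are that one visit decides, that both must succeed, that either suffices with an adjusted level, or that a joint test is used. The article fixes two visits and none of these rules. If the visits disagree, a reader cannot tell from the protocol whether the trial succeeded.

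Two things are at stake. The first is the 5% level, which does not hold if either visit may carry the claim. The second is the question being answered. The Background says the long-term effect on remodeling is unclear, the Discussion faults the earlier study for stopping at 3 months, and treatment runs for 12 months. As written, an effect at 3 months that is gone by 12 months could still be reported as meeting the primary end point.

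**Working it through.** **Inputs.** From the Sample size section: response rates 0.70 and 0.40, power 90%, level 0.05, 1:1 allocation, 10% non-assessable. From the Analysis section: threshold 0.05 for every test. The correlation ρ between the month-3 and month-12 test statistics is not in the article and is assumed. I use 0.5 to 0.8 as the working range and show 0 to 0.95. The value 0.5 is what two changes from a shared baseline have when variances and correlations are equal across visits.

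**Step 1: the plan's own figure.** Take a two-sided test of two proportions with pooled variance under the null, mean rate 0.55:

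n = [1.96·√(2·0.55·0.45) + 1.2816·√(0.7·0.3 + 0.4·0.6)]² / (0.70 − 0.40)²
= (1.379 + 0.860)² / 0.09 = 55.7, so 56 per arm.

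Power at 56 is 90.2%. The total is 112/0.9 = 124.4, in line with the stated 124. The figure reproduces with one two-sided test at the full 0.05, so nothing was set aside for a second primary test.

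**Step 2: success at either visit.** With no effect at either visit and each test at two-sided 0.05, the false-positive rate is P(|Z₁|>1.96 or |Z₂|>1.96). At ρ = 0 this is 1 − 0.95² = 9.75%. Otherwise it comes from the bivariate normal distribution.

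**Step 3: success required at both visits.** By inclusion and exclusion, P(both) = 0.05 + 0.05 − P(either).

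| ρ (assumed) | Either visit | Both visits |
|---|---|---|
| 0 | 9.75% | 0.25% |
| 0.5 | 9.1% | 0.9% |
| 0.7 | 8.3% | 1.7% |
| 0.8 | 7.8% | 2.2% |
| 0.9 | 7.0% | 3.0% |
| 0.95 | 6.5% | 3.5% |

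Both columns approach 5% as ρ approaches 1. All figures are two-sided. False claims of benefit alone under the either-visit rule are 4.5% at ρ = 0.5, against 2.5% for a single test.

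**Step 4: power if both visits are required.** Suppose the planned effect is present at both visits, so each test has 90.2% power at 56 per arm. Joint power at ρ = 0 is 0.902² = 81%. The bivariate normal probability P(Z₁<d, Z₂<d), with d the 90.2% normal quantile, gives 83% at ρ = 0.5, 85% at 0.7 and 86% at 0.8. It regains 90% only when the two results agree almost perfectly.

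**Step 5: what the remedies need.** One named visit, or a fixed testing order, gives 5% with 56 per arm. Splitting the level at 0.025 per visit replaces 1.96 by 2.2414 in Step 1 and gives 66 per arm, or 132/0.9 = 146.7, about 147 to 148 randomized. Keeping 56 per arm would leave 84% power.

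**The case against.** The strongest reply is that the article never says success at either visit is enough. It joins the visits with "and", which could mean that both are required, and the error rate would then be below 5%. This stands, and it is why no single inflated rate can be attributed to the plan. The ambiguity remains, because the both-visits reading does not fit a sample size calculated for one test.

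A reader might infer that the true false-positive rate simply is 8 to 9%. The article does not support that as a flat statement. It needs the either-visit rule and a correlation of roughly 0.5 to 0.77, and neither is in the text. Running a separate test at 0.05 for each visit is itself a reasonable reading of the general threshold, not something the article spells out.

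A reader might also add a responder test at each visit and arrive at a still higher rate. The responder rates appear only in the Sample size section, and no section plans both analyses. The mismatch between a responder-based sample size and a continuous end point is a separate issue.

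It can fairly be said that several passages lean towards 12 months: the treatment period in Study objectives, the loss allowance drawn from 12-month experience, and the long-term rationale. They make a 3-month-only claim less natural, but none names month 12 as decisive.

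Finally, a condensed article may leave the sharing of alpha and the order of testing to an analysis plan. That is fair for the mechanics. Which measurement is the primary end point is a protocol matter, and here the protocol itself sets it at two visits.

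**Conclusion.** The point holds as a badly fixed primary end point: two visits are named, one level is given, one test is powered, and no visit is decisive. That part rests on the text alone and I am confident of it.

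The size is conditional. Under an either-visit rule the two-sided rate lies between 5% and 9.75%, and between 7.8% and 9.1% for assumed correlations of 0.8 down to 0.5. Under a both-visits rule the error is controlled and the cost is power, about 83% to 86% over the same correlations if the planned effect is present at both visits. The article does not say which rule applies. A 3-month-only effect could be reported as success; the article does not say that it would be.

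Because this concerns the primary conclusion and the remedy needs no extra patients, it should be settled before any unblinded data are seen.

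**What to change.** In the Abstract (Methods), Study design and Primary end point sections, name the between-arm difference in LVMI change from baseline to 12 months as the single primary end point, tested at two-sided 0.05. Make LVMI change at 3 months a secondary end point, tested only if the 12-month result is significant. Month 12 is the natural choice because it matches the treatment period and the stated long-term question.

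The cost is a protocol amendment and a registry update, since the trial is ethics-approved and registered. An effect seen only at 3 months could no longer be claimed as the primary result. A both-visits rule would also control error, at the loss of power shown above. Splitting the level would need about 66 per arm.

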### Study objectives

The trial has been designed to investigate the hypothesis that trimetazidine treatment (35 mg twice a day, for 12 months) could significantly improve the left ventricular remodeling, reduce the incidence of MACEs and effectively improve myocardial ischemia in CAD patients undergoing PCI with LVH. The primary objective is to validate that trimetazidine treatment could reduce LVMI and improve ventricular remodeling. The secondary objective is to validate that trimetazidine treatment could reduce the risk of MACEs, as well as improve the symptom of angina and myocardial ischemia.

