### Secondary end points

The secondary end points are the change the symptom of angina and myocardial ischemia, and the 3- and 12-month incidence of MACEs. The symptom of angina will be assessed at baseline, 3- and 12-month follow-up period by Seattle Angina Questionnaire. The improvement of myocardial ischemia and exercise capacity will be measured using exercise electrocardiography test and 6-MWT. The 6-MWT is a sample, low-cost method for estimating exercise capacity and will be performed according to standard procedures [22]. Clinical characteristics and a multipurpose health survey that consists of 36 questions (short form-36, SF-36) will be recorded at baseline, 3 months and 12 months. MACEs are defined as a composite end point of death, myocardial infarction, stroke, recurrent angina, re-hospitalization, change of viable myocardium.

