## Discussion

The study is the first investigator-initiated, prospective study to evaluate the treatment effect of trimetazidine on ventricular remodeling in CAD patients undergoing PCI with LVH. The result of the study will confirm whether trimetazidine improves ventricular remodeling, angina and myocardial ischemia.

Cardiac hypertrophy is a common pathological change in cardiovascular diseases. In the early stage, it is an adaptive response of the heart to the overload. With the development of the disease, the myocardial structure will be disordered and the compliance will be decreased. The mechanism of CAD associated with LVH is a complex process involving multiple factors, such as blood pressure, catecholamine and renin-angiotensin-aldosterone system. It is characterized by hypertrophy of cardiomyocytes and changes in coronary microcirculation. Coronary microcirculation networks are the metabolic site of myocardium, and their lesions can cause the decline of coronary reserve function and the changes of myocardial ultrastructure, which are closely related to the maintenance of myocardial energy metabolism.

Myocardial energy metabolism disorders occur prior to typical morphological changes in ventricular hypertrophy [23]. During the development of cardiac hypertrophy, the energy metabolism of hypertrophic cardiomyocytes changes from aerobic oxidation to anaerobic fermentation. Metabolic therapy is to improve the process of energy metabolism so that cardiomyocytes can get more energy. Trimetazidine is a metabolic agent with a protective effect on cardiomyocytes. It mainly inhibits the oxidation of free fatty acids, activates pyruvate dehydrogenase, increases the oxidation of glucose and the production efficiency of cardiac adenosine triphosphate (ATP), as well as maintains myocardial contractile function [24]. It also directs free fatty acids to synthesize phospholipids, which involve in the construction of cell membrane. Accordingly, by improving the environment of the cell and promoting the construction of membrane, trimetazidine might protect the ultrastructure of myocardium and is likely to inhibit or even reverse the cardiac hypertrophy.

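### The protocol sets out to validate the secondary end points under one undivided p < 0.05, although the trial is sized on LVMI alone; they should be labelled supportive (minor)

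*Protocol article*

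**What the plan says.** All references are to the protocol article.

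- **Study objectives.** The primary objective is to validate an effect on LVMI and ventricular remodeling. For the second tier the wording runs: "to validate that trimetazidine treatment could reduce the risk of MACEs, as well as improve the symptom of angina and myocardial ischemia". The opening hypothesis of that section also names MACEs and myocardial ischemia alongside remodeling.
- **Study design.** Four secondary measures are named: "Seattle Angina Questionnaire, myocardial ischemia measured by 6-MWT and exercise electrocardiography test, as well as MACEs".
- **Secondary end points.** For angina: "The symptom of angina will be assessed at baseline, 3- and 12-month follow-up period by Seattle Angina Questionnaire". For events, the end point is "the 3- and 12-month incidence of MACEs". Table 1 schedules the 6-minute walk test and the exercise ECG test at both follow-up visits.
- **Sample size.** The calculation uses response rates of 70% and 40% for LVMI improvement. No secondary end point enters it.
- **Analysis.** Chi-squared, t and log-rank tests are listed, followed by a single rule: "A *p*-value < 0.05 will be considered significant". The rule does not distinguish primary from secondary end points.
- **Discussion, first paragraph.** "The result of the study will confirm whether trimetazidine improves ventricular remodeling, angina and myocardial ischemia". MACEs are not in that list.

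**The concern.** The labels primary and secondary are in place, but the stated aim and the stated decision rule treat both tiers alike. Both are to be validated, and both are judged at 0.05. The text does not make a secondary claim depend on the LVMI result and does not describe the secondary end points as supportive.

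The practical risk is a trial in which LVMI is null, one of several secondary tests falls below 0.05, and the report states that an effect on angina, ischemia or MACEs has been validated. The protocol's wording would permit that sentence. The probability of such a result for an ineffective drug would exceed the 0.05 that a reader would attach to it.

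**Working it through.** **1. What the design is sized for.** Inputs from Sample size: 70% against 40%, alpha 0.05, power 90%, allocation 1:1. With a pooled-variance two-proportion formula, two-sided:

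n = [1.960 × √(2 × 0.55 × 0.45) + 1.282 × √(0.70 × 0.30 + 0.40 × 0.60)]² / 0.30² = (1.379 + 0.860)² / 0.09 ≈ 55.7, so 56 per group.

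Adding 10% gives 56 × 1.1 = 61.6, rounded up to 62 per group, or 124 in total. The stated figures are reproduced. They correspond to a two-sided 0.05 for LVMI response, and nothing in them relates to the secondary end points. A two-sided 0.05 per test is therefore used below.

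**2. How many secondary tests.** The protocol does not fix this, so two counts are carried:

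- *Four tests*: Seattle Angina Questionnaire, 6-minute walk, exercise ECG test and MACEs, once each.
- *Eight tests*: the same four, each at 3 and 12 months (4 × 2).

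Seven is also possible, if MACEs are compared by one 12-month log-rank test and the other three at both visits (3 × 2 + 1). Several questionnaire scales or exercise ECG measures would raise the count.

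**3. Independent tests, no true effect on any of them.** The chance of at least one p < 0.05 is 1 − 0.95^k:

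- k = 4: 1 − 0.95⁴ = 0.185
- k = 7: 1 − 0.95⁷ = 0.302
- k = 8: 1 − 0.95⁸ = 0.337

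Counting only results in favour of trimetazidine, the chance is 1 − 0.975^k: 0.096 for k = 4 and 0.183 for k = 8.

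**4. Correlated tests.** The protocol gives no correlations, so a range is assumed. These are simulated multivariate normal test statistics with critical value 1.96:

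| Tests | Assumed correlation | Any p < 0.05 | In favour of trimetazidine only |
|---|---|---|---|
| 4 | 0 | 0.185 | 0.096 |
| 4 | 0.5 throughout | 0.156 | 0.078 |
| 4 | 0.7 throughout | 0.13 | 0.065 |
| 8 | 0 | 0.337 | 0.183 |
| 8 | 0 between end points, 0.5 between visits | 0.32 | 0.17 |
| 8 | 0.5 throughout | 0.25 | 0.125 |
| 8 | 0.7 throughout | 0.19 | 0.095 |

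A more extreme structure for eight tests (0.7 between end points, 0.9 between visits) gives about 0.18, so the lower end is not sensitive to the exact pattern.

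**5. Comparison with the nominal level.** The smallest two-sided figure, 0.13, is 2.6 times 0.05. The smallest benefit-only figure, 0.065, is 2.6 times the 0.025 that a single two-sided test allows in that direction.

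**The case against.** The strongest reply is that this is analysis-plan material. The article condenses a fuller protocol, the SAP is not shown, and the ordering or adjustment of secondary end points is commonly left there. That stands as far as it goes: the absence of a multiplicity procedure is not the point here. What remains is what the article itself states, namely an aim to validate the secondary effects beside one undivided significance rule. An SAP that called these end points supportive would not match that stated objective.

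Second, the tone elsewhere is more cautious. The abstract says only that the drug might reduce MACEs, and the Background speaks of trying to investigate this. The first Discussion paragraph says *confirm whether*, which is neutral, and omits MACEs; the closing paragraph limits confirmation to ventricular remodeling. A reader might infer that every secondary end point is declared confirmatory throughout. The documents do not support that; the claim rests mainly on the verb in Study objectives.

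Third, a reader might infer that the plan commits to at least eight tests and hence to a false-positive rate of about 25%. The documents do not support that either. Data are collected at two visits, but the Analysis section does not say that each visit is tested separately, and the 12-month log-rank comparison may be the only MACE test. The 25% also needs an assumed correlation of 0.5, and it counts results in either direction. For false claims of benefit the matching figure is 12.5%.

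Fourth, nothing says that one significant result is enough. The objective joins its parts, and a requirement that all succeed would not inflate the error. This is fair, but the text fixes neither reading, so the permissive one is available at reporting.

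Finally, uncontrolled secondary tests are acceptable when read as supportive. That is true, and saying so in the protocol would settle the matter.

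**Conclusion.** The point holds in a narrow form and is minor. The aim of validating effects on MACEs, angina and ischemia is stronger than the design supports, since the trial is sized on LVMI only and a single undivided 0.05 applies to every comparison.

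With no true effect on any secondary end point, the chance of at least one nominally significant secondary result is about 13% to 19% for four tests and about 19% to 34% for eight. The chance of a false claim of benefit is about 7% to 18% across both counts. These ranges assume two-sided tests at 0.05, common correlations from 0.7 down to 0, and that any one significant result could be presented as validation. The protocol states no family-wise error rate, no correlations and no fixed number of tests, so no single percentage should be quoted. The primary LVMI inference and the sample size are not affected.

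**What to change.** - **Analysis:** state that the p < 0.05 decision rule applies to the primary LVMI comparison, and that the secondary end points are supportive and reported as estimates with 95% confidence intervals.
- **Study objectives:** for the secondary objective, replace *validate* with *explore* or *assess*.
- **Discussion, first paragraph:** limit the confirmatory statement to ventricular remodeling, as the closing paragraph already does.

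If the sponsor wants formal secondary claims, an optional alternative is a pre-specified fixed sequence of 12-month results. Each would be tested at two-sided 0.05 only after a significant primary result, stopping at the first non-significant one, with the 3-month results descriptive.

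The main change is wording only: no extra patients, no extra data and no change to the sample size. Its cost is that an isolated secondary p < 0.05 could no longer be reported as validated.
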